## Abstract

**Background:**

Podcasts have proven to be a successful alternative source of educational material for students. Given the ability to listen to podcasts 24/7 and while on the go, this technology has the potential to provide informative and educational material to a large number of people at any given time. Podcasts are usually freely available on commonly used mobile devices, such as smartphones, laptops, and tablets.

**Objective:**

This paper describes the impact of health-related podcasts as an intervention tool to support the knowledge and awareness of nursing students on a given topic.

**Methods:**

Pre- and postpodcast questionnaires will gather data regarding the participants’ knowledge and awareness of two topics—gestational diabetes and mental health. This intervention will be tested on general nursing undergraduate students. The total number of students (N=2395) from the participating universities are broken down as follows: (1) University College Cork (n=850) and the University of Galway (n=450) in Ireland, (2) Mzuzu University in Malawi (n=719), and (3) University of Fort Hare in South Africa (n=376).

**Results:**

The study received ethical approval from the University College Cork Ethics Committee (2022-027A1). The approval obtained from University College Cork sufficed as ethics coverage for the University of Galway in Ireland. Ethics approval was also received from the Mzuzu University Research Ethics Committee (ID MZUNIREC/DOR/23/28) and the Inter-Faculty Research Ethics Committee of the University of Fort Hare (ID CIL002-21). Data collection is currently underway and will continue until the end of February 2024. The quantitative and qualitative data are expected to be analyzed in March 2024.

**Conclusions:**

Results from this study will allow for an investigation into the impact of podcasts in different settings: a high-income country (Ireland), an upper-middle–income country (South Africa), and a low-to-middle–income country (Malawi). The data gathered from this feasibility study will provide more clarity on the potential utility of podcasts as an intervention tool. We will gather data regarding listener demographics (eg, country of residence, age, gender, and year of study).

**International Registered Report Identifier (IRRID):**

DERR1-10.2196/50735

## Introduction

### Overview

The term “podcast” has been used since approximately 2004. It originally stemmed from 2 terms “iPod” and “broadcast” [1]. The groundbreaking iPod device from Apple pioneered the mobility of digital audio information. Although the iPod has never been the only device used for podcast listening, it swiftly grew into one of the most prominent listening devices [2]. A podcast can be listened to on any digital audio listening device, including a computer that supports audio file playing. Therefore, podcasts can be listened to 24/7 and while on the go. These combined attributes have dramatically increased the use of podcasts over the last 20 years [3]. During this period, podcasts have been regarded as effective medical educational instruments [4,5]. Thus, the accessibility and open access of podcasts may be hugely attractive to higher education institutes as a method of teaching and learning.

Chin et al [6] (2017) showed that after listening to the extracurricular audio podcasts on health-related topics, students who completed the study experienced a significant and probably educationally relevant improvement in their knowledge. This aligns with the results of Mitchell et al [7] (2021), which showed an overall increase of 11.54% in knowledge attainment in undergraduate nursing students after listening to a podcast on delirium [7]. Overall, these studies demonstrate the impact of podcasting on knowledge attainment in third-level education.

A study of the literature in 2017 further highlights that podcasts are a popular source of educational material for a wide range of health care professionals, including junior doctors, nurses, and medical students [4]. In particular, third-level nursing education is an area of health care that calls for sophisticated critical thinking abilities and decision-making processes, which may likely influence clinical competency. University staff members can find themselves searching for new and creative ways to present material in an engaging fashion as the demands on their time and the availability of innovative tools for use in nursing education expand. The implementation of podcasting in nursing education is one strategy to enhance learning, as discussed in the literature. Recent research conducted in Northern Ireland on podcasting to improve undergraduate nursing students’ awareness of Parkinson Disease found that “podcasting as an educational resource for undergraduate student nurses is a successful way of developing knowledge for PD [Parkinson disease]” [8].

There has been a rise in research being conducted on podcasting in nursing education [9]. Despite this, there is limited research being undertaken on the use of podcasts in Africa, even though podcasting is a great topic of conversation among interested African communities. Surveys completed by the Reuters Digital News Report that included 2 African countries highlighted that 33% of participants were considered regular podcast users [10]. Notably, 50% believed that podcasts are more informative in terms of providing a better understanding of issues compared to traditional media platforms [10].

This research will allow for an investigation into the impact of podcasts on knowledge and awareness in different settings—a high-income country (Ireland), an upper-middle–income country (South Africa), and a low-to-middle–income country (Malawi).

Knowledge and awareness have often been used synonymously, but in this study, a distinction between these 2 interchangeable words is set. Knowledge has been described as “the fact or condition of knowing something with familiarity gained through experience or association,” the “acquaintance with or understanding of a science, art, or technique,” and “the range of one's information or understanding” [11]. Awareness has been described as “knowledge and understanding that something is happening or exists” [12]. In our study, awareness will be defined as having heard of a term or topic, while knowledge will be defined as a deeper understanding of the area.

The podcast topics are as follows:

#### Pregnancy

According to the World Health Organization (WHO), approximately 800 women died every day from pregnancy and childbirth-related avoidable causes in 2020 [13]. Of note, nearly 95% of these maternal deaths took place in low- and low-to-middle–income countries, such as Malawi [13]. This highlights the need to raise awareness of pregnancy risk factors, complications, and services available for women to access the care they need.

#### Gestational Diabetes

The WHO describes gestational diabetes as “hyperglycemia with blood glucose values above normal but below those diagnostic of diabetes,” which occurs during pregnancy [14]. Worldwide, 21.3 million pregnancies are linked to hyperglycemia, and of these, 18.4 million pregnancies are linked to gestational diabetes mellitus [15]. Furthermore, it is estimated that more than 90% of hyperglycemia cases in pregnancy occur in low- and middle-income countries [16]. Gestational diabetes can impact both the fetus and the mother. Long-term implications for children include an increased risk of obesity and metabolic disruption [17]. Furthermore, women who experience gestational diabetes are at risk for developing type 2 diabetes later in life [17]. This demonstrates that gestational diabetes a potentially preventable condition can have a huge societal burden and devastating long-term outcomes.

#### HIV/AIDS

The WHO figures highlight how HIV infection remains a significant global health concern with 40.1 million deaths occurring to date [18]. Approximately, 650,000 persons died in 2021 as a result of HIV-related causes, and by the end of 2021, an estimated 38.4 million people were living with HIV [18]. Nearly 60% of new HIV infections worldwide occur in the WHO African Region [18]. The HIV infection is incurable. However, owing to accessibility to effective HIV prevention, diagnosis, treatment, and care, especially for opportunistic infections, HIV infection has evolved into a manageable chronic health disease, allowing those who have it to live long and healthy lives. Unfortunately, the disease continues to take many lives despite the availability of treatment and hence it is an important podcast topic to discuss to increase knowledge and awareness.

#### Cervical Cancer

According to global estimates, there were 604,000 new cases and 342,000 deaths from cervical cancer in women worldwide in 2020 [19]. New cases of cervical cancer and deaths from cervical cancer that occurred in low- and middle-income countries accounted for around 90% of the global total deaths in 2020 [20]. Nearly 50% of high-grade cervical precancers are caused by 2 human papillomavirus types (16 and 18) [20]. This is an important topic to discuss as cervical cancer is curable if detected early and treated effectively. Preventing cervical cancer is more affordable with the human papillomavirus vaccine, precancer lesions screening, and treatment.

#### Malnutrition

The WHO defines malnutrition as “undernutrition (wasting, stunting, underweight), inadequate vitamins or minerals, overweight, obesity, and resulting diet-related noncommunicable diseases” [21]. A total of 462 million adults are underweight, compared to 1.9 billion who are overweight or obese [21]. Undernutrition is a contributing factor in about 45% of deaths in children younger than 5 years and mostly takes place in low- and middle-income countries [21]. The prevalence of childhood obesity and overweight is also rising in these same nations. The global burden of malnutrition has substantial and long-lasting effects on people and their families as well as on communities, nations, and the economy; therefore, greater conversation around this area is imperative.

#### Mental Health

As evidenced by the inclusion of mental health in the United Nations Sustainable Development Goals [22], there has been growing recognition of the crucial role mental health plays in achieving global development goals in recent years [23]. According to Arias et al [24] (2022), 418 million disability-adjusted life years or 16% of all disability-adjusted life years worldwide could be attributed to mental diseases in 2019. Overall, this confirms that the need for action on mental health topics is paramount.

### Objective of the Feasibility Study

This paper explores the impact of health-related podcasts as an intervention tool to support the knowledge and awareness of nursing students on a given topic. To address this objective, we aim to answer the following questions:

Can podcasts support listeners' knowledge of global health topics?Is knowledge attainment from podcasts different across Ireland, South Africa, and Malawi?Is podcasting effective for supporting awareness in nursing students on global health diseases and issues?

## Methods

### Research Design

This pre- and postpodcast intervention is a feasibility study. Feasibility studies facilitate researchers’ evaluation of whether an intervention is suitable to undergo additional investigation or whether the concepts and conclusions can be applicable and sustainable to the population [25]. A feasibility method was chosen for this study due to the lack of previously published studies on this specific intervention.

### Type of Study and Setting

This study mainly involves quantitative data, but qualitative data will be synthesized for the 1 open-ended question on the survey tool. These questionnaires will be created and managed using Google Forms, as it is compliant with the General Data Protection Regulation. Microsoft Excel will be used to capture qualitative and quantitative data and to execute descriptive statistics in the form of percentages and frequencies [26]. This study will be carried out from March 2023 until March 2024.

The selected podcast topics revolve around global health concerns that exhibit significant variations in understanding and practices across different countries. This is intended to enable in-depth podcast discussions and survey questions that can yield insights into how nursing students use the podcasts. These podcast topics have been chosen to encompass a diversity of health-related topics affecting both high- and low-income countries.

To date, the recordings of the podcasts have been conducted. Video and audio files for 2 out of the 6 podcasts will be available for the study participants. Despite only 2 podcasts being chosen for research purposes, all 6 podcasts will be disseminated on platforms including but not limited to YouTube and Spotify. The podcasts’ duration ranges from approximately 30 to 60 minutes each. Each podcast discusses the risk factors, symptoms, and treatment or management of the global health topic.

Each podcast was created with a panel of international experts along with a chair (AD and BC). The 2 podcasts selected for the study are the gestational diabetes podcast and the mental health podcast. As this is a voluntary feasibility project, we only have the resources to examine 2 of the podcasts. Upon completion of this research, we will determine if podcasting is an effective method of increasing knowledge and awareness attainment. If the results are positive, we will conduct a broader survey, which will include members of the public and not just nursing students, and will release more podcasts. In addition, mental health and gestational diabetes are widespread issues normally taught in depth in nursing schools and are not confined by geographical locations or socioeconomic status. Likewise, these podcasts had the best audio quality, conversation flow, and in-depth discussion, as decided by the research team. It is evident from the literature that gestational diabetes is a global phenomenon that can impact people from Ireland, South Africa, and Malawi and have potentially long-term preventable implications [16,17]. Similarly, mental health is a global health concern that is gaining increasing attention due to the addition of mental health in the Sustainable Development Goals and the disability-adjusted life years that are attributable to mental disease [23,24]. The selected global health topics are on the list of the top 10 global public health challenges to track in 2023 [27].

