### Data Collection and Management

Questionnaires will be made using Google Forms, which are stored on UCC’s Microsoft OneDrive. The questionnaires will include closed-ended questions using a point scale, with points given to the tick-the-box answers of “Yes”, “No,” or “I don’t know.” These questionnaires will be distributed to UCC (Ireland), University of Galway (Ireland), University of Fort Hare (South Africa), and Mzuzu University (Malawi). Regarding the data collection, the investigators will not seek names or emails from the participants, and the data will be fully anonymized. Fully anonymized data are achievable in this study, as participants are not required to complete two different surveys. The pre- and postpodcast questions are on a single Google Form, separated only by the embedded podcast file (not 2 separate survey forms), allowing a direct comparison of survey responses without requiring participant contact details. Once the survey is submitted, the option to withdraw will no longer be available. Answers to our survey (questionnaires) will be stored on UCC-supplied Google Forms and uploaded to OneDrive. Data on knowledge and awareness will be collected from both pre- and postpodcast surveys. Information on gender, age, year of study, and the university the student is attending will also be stored, along with the consent forms. The UCC-supplied OneDrive will also be used during data collection and data analyses due to the ability to store data generated on the cloud automatically. Data will be stored for a minimum of 10 years. The data will be controlled by the UCC study members. General Data Protection Regulation will be observed at all times with all information anonymized.

Data collection tools will be structured according to the research themes outlined as follows:

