### Strengths and Limitations

The role of social media platforms as a medium to deliver education has been under development for several years. This research will provide a clear contribution focusing on the impact of one such platform—YouTube—for undergraduate nursing students in the areas of knowledge and awareness on a set of given topics. This research is international and will enable a greater understanding of the usefulness of podcasts in a high-income country (Ireland) compared to middle-to-low-income countries (South Africa and Malawi). Nonresponse is one of the limitations of this study. Pre- and postpodcast questionnaires are planned to be administered before and after listening to a podcast recording. This may cause participants to become mentally fatigued and not fill out the questionnaire following the podcast, resulting in a reduced response rate. Another limitation of this study is selection bias. For this study, only general undergraduate nursing students will be used to gather information, and thus, they could skew the results due to the level of knowledge they should already have from their undergraduate studies. The generalisability of the study may be limited by the cohort only being composed of nursing students.

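### The article describes no item showing whether a respondent played the podcast or had heard it before, so every submitted form is analysed as unexposed before and exposed after

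*Protocol article*

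**What the plan says.** Data Collection and Management fixes the layout of the form: "The pre- and postpodcast questions are on a single Google Form, separated only by the embedded podcast file". The same section lists what is kept. On outcomes: "Data on knowledge and awareness will be collected from both pre- and postpodcast surveys". On background: "Information on gender, age, year of study, and the university the student is attending will also be stored", together with the consent forms. Measurement Tools adds one open comment question. Neither section describes an item on listening.

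Inclusion and Exclusion Criteria screens on internet access, residence, registration as a general nursing student, consent and age. It removes neither students who skip the recording nor students who already know it. Data Analysis makes the pretest the control, uses a paired two-tailed t test and reads a higher posttest mean as evidence that the podcast worked. No exposure condition enters.

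On availability, Type of Study and Setting says that "all 6 podcasts will be disseminated on platforms including but not limited to YouTube and Spotify", and also that "The 2 podcasts selected for the study are the gestational diabetes podcast and the mental health podcast". The two study episodes are therefore part of the announced public release. No release date is given. The study period is given: "This study will be carried out from March 2023 until March 2024".

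**The concern.** The only comparison in this study is each student's score before against the same student's score after. It measures the podcast only if the student had not heard the episode at the first score and had heard it by the second. The plan as described checks neither condition.

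The second condition is the weaker one. The recording is long, it sits between two blocks of tick-box questions, and nothing described stops a respondent from moving straight to the second block. Strengths and Limitations foresees mental fatigue, but only as a reason for leaving the posttest blank. Skipping the recording and submitting anyway takes less effort and leaves no trace in the data. The form is anonymous, so exposure cannot be established later.

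Two of the three questions in Objective of the Feasibility Study are directly affected. The first asks about the knowledge of listeners, who cannot be identified. The second compares countries, so different skipping rates could by themselves produce a difference. The decision to go on to a broader survey and more podcasts is tied to positive results. A small gain could mean that the podcast teaches little or that few students played it, and those two readings call for different next steps.

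**Working it through.** The documents state no sample size, expected gain or SD for this study, so there is no figure of the plan's own to reproduce. The check has two parts.

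**Reading the sections together.**
- Form layout: only the podcast file lies between the two question blocks.
- Recorded data: answers before and after, gender, age, year of study, university, consent, one free comment.
- Exclusions: none by exposure.
- Analysis: all pairs, pretest as control.
- Identifiers: none.

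Under the plan as described, a skipper, a partial listener, a prior listener and a full first-time listener all enter the t test alike.

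**Illustrating the size.** Inputs:
- 27 knowledge items for gestational diabetes (Measurement Tools).
- An 11.54% increase, taken from the earlier delirium podcast study cited in the Introduction. It is not a design assumption of this trial.
- s, the share who skip, and c, the share who had already heard the episode. Both are assumed, because the documents give no value.

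If 11.54% means percentage points of the maximum score, the gain is 0.1154 × 27 = 3.12 items. If it means a relative increase, the gain depends on the baseline score and is smaller: for an assumed baseline of 13.5 items it would be 0.1154 × 13.5 = 1.56.

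1. *Skippers gain nothing.* Observed gain = (1 − s) × true gain. With 3.12 items:
   - s = 20%: 0.8 × 3.12 = 2.49
   - s = 40%: 0.6 × 3.12 = 1.87
   - s = 60%: 0.4 × 3.12 = 1.25

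   (The products use the unrounded 3.1158.)

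2. *Everyone also gains r from seeing the questions twice.* Write d for the podcast's own effect. Then observed gain = (1 − s) × d + r, and the error against d is r − s × d. It is zero when r = s × d. With d = 3.12 and s = 40%, that is r = 1.25 items. A smaller r leaves the podcast's effect understated, and a larger r leaves it overstated. A retest gain is plausible: one sample awareness question asks whether the student has heard of metformin, and having just read the word at pretest may turn the second answer into a yes.

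3. *Countries with equal true effect but unequal skipping.* With no retest gain, 10% against 40% skipping gives 11.54 × (0.90 − 0.60) = 3.46 percentage points of apparent difference, where the true difference is zero.

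4. *Prior listeners added, also gaining nothing and independent of skipping.* The factor is (1 − c)(1 − s). For c = 10% and s = 10% it is 0.81. For c = 20% and s = 25% it is 0.60.

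**The case against.** The strongest reply is that the questionnaire itself is not shown. Table 1 in the article gives only sample questions. The sentence on stored information is not a full inventory either: the Conclusions say that country of residence will be gathered, and that sentence does not list it. Type of Study and Setting also hopes for insight into how students use the podcasts, which leaves room for usage items. This stands. A reader might infer that the form records no listening at all. The article supports only the statement that no such item is described.

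Second, public release is announced in the future tense and without a date. A reader might infer that the episodes were open to students during collection and that the pretest is contaminated. Nothing says so. The remark in Strengths and Limitations, "This research will provide a clear contribution focusing on the impact of one such platform—YouTube—for undergraduate nursing students", concerns the delivery medium, not early release. Prior exposure is therefore a possibility only.

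Third, a reader might conclude that the bias must run towards zero. Step 2 of the check shows that it need not. The shares s and c have no source, and the cited 11.54% can be read in two ways. Different skipping rates between countries are likewise possible, not shown.

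Fourth, analysing everyone who submits is a defensible estimate of what offering the podcast achieves, and an analysis of self-declared listeners brings in selection, since keener students may both listen more and learn more. This also stands, and it is why the main analysis should not change.

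These points do not remove the core. The described exclusions and analysis make no use of listening, the stated question is about listeners, and the information is lost once an anonymous form is submitted. That goes beyond detail an article would normally leave out.

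**Conclusion.** The point holds in a limited form. As described, the plan cannot distinguish a podcast that does not teach from one that was not played. Skipped listening is the main problem and does not depend on public release. Prior exposure is secondary and only possible.

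The direction of the bias is not determined: skipping lowers the gain, while a retest effect is credited to the podcast. The size is unknown because s is not known to be recorded. The figures of 2.49, 1.87 and 1.25 items assume a true gain of 3.12 items, no gain in skippers and the stated values of s. The 3.46-point country difference assumes 10% against 40% skipping and no retest gain. They show scale and are not estimates for this study. This is a cheap improvement worth making, not a fault that invalidates the design.

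**What to change.** For forms not yet submitted:
- Before the pretest, add one yes/no item on whether the student has already listened to this podcast.
- Before the posttest, add one item on how much was heard: all, most, some or none.
- Keep all submitters as the main analysis, so that forms with and without the new items are treated alike.
- Add one sensitivity analysis restricted to respondents with no prior listening who report all or most.
- Report the listening share per university as a feasibility outcome. It also shows whether a country difference could reflect different uptake.
- If the two study episodes are not yet public, hold their release until collection closes at the end of February 2024.

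The cost is two tick-box questions, one extra analysis and, where still possible, a delay for two episodes. Anonymity is unaffected. The downsides are that listening is self-reported, that listeners select themselves, and that the items will be missing for forms already submitted, since collection is under way. Strengths and Limitations should say this. If the form can no longer be changed, it should at least state that listening was not verified and that prior exposure cannot be ruled out.
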